### Primary outcome measure

Network connectivity among multiple brain regions and neuroimaging biomarkers with the 2.5 years’ follow-up at 0.5 year interval. [Time Frame: subjects will be assessed six times (once half a year, up to 2.5 years)]Differences in macro-structural and micro-structural network connectivity among healthy controls, prodromal diabetes and diabetes will be evaluated. These MRI measures include volumetric characteristics (e.g., hyper-intensities, white matter lesions, atrophy), quantitative measures (e.g., T2 relaxation times, mean diffusivity, fractional anisotropy, mean kurtosis), functional characteristics (e.g., activated regions, cerebral blood flow), network properties (e.g., functional and structural connectivity, graph-theoretical measures). [Time Frame: subjects will be assessed six times (once half a year, up to 2.5 years)]

### Secondary outcome measures

*Evaluation of obesity and the changes in the state of obesity at 2.5 years*. Simple evaluation of obesity will include: body mass index will be calculated as the weight (kg) divided by the square of the height (m^2^). Waist circumference will be taken as the minimum circumference between the umbilicus and xiphoid process and measured to the nearest 0.5 cm. [Time Frame: subjects will be assessed six times (once half a year, up to 2.5 years)]*Metabolic characteristics and their changes at 2.5 years*. Simple metabolic characteristics will include: oral glucose tolerance test, C peptide releasing test and insulin releasing test, homeostasis model assessment of insulin resistance,insulin secretion of homeostasis model assessment and homeostasis model assessment-β. What’s more, cardiovascular risk factors (e.g., albumin, creatinine, total cholesterol, low density lipoprotein (LDL)- and high density lipoprotein (HDL)-cholesterol, triglycerides, glycosylated hemoglobin) will be assessed. [Time Frame: subjects will be assessed six times (once half a year, up to 2.5 years)]*Mental health and the changes in the scores of the scales at 2.5 years*. To evaluate the mental health, a series of psychiatric evaluation scale (e.g., MMSE, MoCA,HAS, SDS, WHOQOL) will be assessed. [Time Frame: subjects will be assessed six times (once half a year, up to 2.5 years)]*Lifestyle and its changes at 2.5 years*. Lifestyle specifics, including alcohol consumption, smoking behavior and mobility and exercise habit will be obtained. At the same time, quality of life will be obtained through a questionnaire. [Time Frame: subjects will be assessed six times (once half a year, up to 2.5 years)]

## Discussion

The current study evaluates various characteristics of diabetes, especially the central nervous system image presentations in different stage of diabetes progression, and aims to establish an imaging evaluation system for detecting and evaluate MCI in diabetes. Benefits and limitations of this study are discussed below.

It is reported by most researchers that diabetes result in regional hypoperfusion. However, Henry Rusinek and his colleagues found that no hypoperfusion exists in diabetes group, in contrast to hypoperfusion in insulin resistant but not diabetes group [29]. Since insulin resistant is one of main mechanisms of diabetes, we are still uncertain why the perfusion data differs between the two groups. The current study will follow up individual’s characteristics in various areas, especially the image presentation for not less than 3 years. Natural progression of diabetes is monitored. Reperfusion or compensation result in diabetes will be explored. We may discovery the unrevealed mechanism for the divergent between IR and diabetes group.

Structure changes are common in advanced T2DM. It may also exist at prediabetes stage. The volume changes should be used to be one of the covariant to prevent its effect to signal intensity. In current study, we take cerebral ventricle volume, which may represent the structure changes of the whole brain, as a covariant. DKI reveals the non-Gaussian characteristics of gray and white matter [31]. Imaging reports of this respect in diabetes are limited. We undergo the examination of DKI, instead of DTI to explore the real world of microstructure.

Various imaging researches of diabetes have been reported. Most of them are studies of one or two protocols. In our study, multi-modal sequences will be conducted and analyzed at the same time. It may be revealed which one or combined protocols may express the highest area under curve by drawing ROC curve. Corresponding sensitivity and specificity are calculated, and then we will get the cutoff values to diagnose MCI.

MoCA is verified to be a valid scale for MCI in diabetes in China [32]. Different dimensions scores of MoCA will be calculated and analyzed together with imaging presentations. Therefore, we may detect the functional node for different cognitive dimensions. The association may help to speculate prognosis. The neuropsychological test battery comprises another four scales. They test the condition of cognition, affection and life style. Different cognitive-related circuits overlap and interact significantly. Therefore, affective and life style state evaluation is necessary for matching the changes of cerebral functional imaging presentations.

Treatment strategies vary significantly. According to our preliminary experiment, patients took metformin either alone or in combination with other drugs. Some of the diabetes went on insulin treatment. Part of the prediabetes group took statin-related drugs. Antihypertensive drugs were also taken by some individuals to control their blood pressure. Medications related to cardiovascular disease affect cerebral perfusion significantly [27], and they may play a role in neuronal plasticity as well [26]. In the current study, we have not taken medication therapies as covariant for some practice and ethics issues. The reliability of results may be affected by the disaccord of medication therapies.

Future studies should focus on comparing the imaging characteristics between MCI converted group and no converted group. Gene type may serve as a control condition. Other techniques such as using MRS for the metabolic data could be useful and should be evaluated as well. The consistency of therapeutic regimen should also be guaranteed.

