Previous studies suggested that the brain microvascular alterations might explain MCI. A positron emission tomography-computed tomography study revealed that the focal brain blood decrease occured at as early as several years before Alzheimer`s disease diagnosis and was accompanied with the MCI progression [16]. On the contrary, a trend to a slight cerebral blood flow (CBF) increase in bilateral hippocampi and the posterior cingulate gyrus among patients with MCI was noticed using dynamic susceptibility contrast MRI [17]. The major shortcoming of these methods to measure CBF is the use of radio-labeled contrast agents, thus, not suitable for screening brain microvascular alterations in the prodromal diabetic population. Three-dimensional pseudo-continuous arterial spin labeling (3D-pCASL), a non-invasive and non-contrast perfusion imaging method [18], is commonly used to measure CBF alterations and demonstrates equivalent diagnostic performance to Single-photon emission computed tomography (SPECT) for Alzheimer`s disease [19].

Thus, we designed the current prospective diagnostic trial for 2 purposes. First, to investigate the structure, functional alterations and gray/white matter integrity with sMRI, fMRI and diffusional kurtosis imaging (DKI, also measures non-Gaussian diffusion and may provide additional and complementary information to DTI [20]) in prodromal diabetic population, respectively. Second, to investigate the early brain microvascular alterations by using 3D-pCASL.We hope to establish an integrated diagnosing system for early MCI in prodromal diabetic population by using multimodal MRI techniques.

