### Sample size calculation and statistics

Power calculations have been estimated with reference to other studies that used similar end points [21, 29], according to the formula for estimating the variances of mean values from multiple groups [29]. A sample size of 40 patients per group will be suitable with a power of 0.8, an alpha significance level of 0.05 (two-side). In our group, longitudinal changes of this effect size have been shown previously in groups larger than 10 subjects. Given a drop-out ratio of included subjects, at 25 %, into account, the total sample size is 53 in each group.

Demographic clinical, laboratory, cognitive, and neuropsychological data will be analyzed using SPSS 22.0 (SPSS, Inc.). One-way analysis of variance or *χ*^2^ test will be used to explore differences of these data among three groups (HC, prodromal diabetes and diabetes). Neuropsychological difference among them will be performed with analysis of covariance (ANCOVA) using demographic factors (gender, age, and years of education) as covariates. *Post-hoc* comparisons will then be performed with all demographic factors (gender, age, and years of education) as covariates. *P* < 0.05 is considered as significant. It is reported ReHo and ALFF values are affected by the structure alterations (e.g., atrophy) [30]. We will take ventricular volume as a covariance to rule out such influence.

For images analysis, one-sample t tests will be performed on the individual corresponding maps for each group using SPM12 to explore the differences within groups. Dunnett-*t* test will be performed for differences among case groups and healthy control group. The statistical threshold of the two test will both be set at *P* <0.005 which corresponded to a corrected *P* <0.005 (multiple comparisons with family-wise error).

Linear regression analysis is performed across the T2DM groups and prediabetes groups to assess relationships between imaging values and cognitive testing scores. When the most sensitive parameters are found, a receiver operating characteristic (ROC) curve will be generated to achieve the sensitivity and specificity of the certain parameter for early detection of the cognitive decline.

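### Choosing the best single or combined MRI protocol by the highest AUC ranks paired estimates without their uncertainty and favours combinations

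*Protocol article*

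**What the plan says.** The Background gives the aim: "We hope to establish an integrated diagnosing system for early MCI" in people with prodromal diabetes, using several MRI techniques.

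The section on sample size and statistics describes two steps. First: "Linear regression analysis is performed across the T2DM groups and prediabetes groups to assess relationships between imaging values and cognitive testing scores". Then: "When the most sensitive parameters are found, a receiver operating characteristic (ROC) curve will be generated", from which sensitivity and specificity are read.

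The Discussion adds how protocols are to be compared: "It may be revealed which one or combined protocols may express the highest area under curve by drawing ROC curve". It continues: "Corresponding sensitivity and specificity are calculated, and then we will get the cutoff values to diagnose MCI".

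The sample size comes from a formula for means across several groups, with 40 per group for 80% power at a two-sided 5% level. After allowing for loss: "Given a drop-out ratio of included subjects, at 25 %, into account, the total sample size is 53 in each group". The calculation refers to no AUC, AUC difference, sensitivity or specificity. The article describes no interval or test for a difference between AUCs.

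**The concern.** Every participant has all four sequences, so the AUCs of the sequences and of their combinations are paired. Taking the largest observed value says nothing about whether it differs from the next one. Two problems follow.

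- **Chance ranking.** With few MCI cases, the sampling error of a paired difference can be as large as a plausible true difference, so a sequence can come first by luck.
- **Built-in preference for combinations.** If a combination is fitted and scored on the same subjects, adding sequences nearly always raises its apparent AUC. The rule then tends to favour the multimodal protocol whether or not the extra sequences carry information.

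The cut-offs for diagnosing MCI are to follow from this ROC step, so an error in the ranking carries into the diagnostic rule that the trial hopes to deliver.

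**Working it through.** **The plan's own figure.** 40 / (1 − 0.25) = 53.3, against 53 stated; conversely 53 × 0.75 = 39.75. The inflation reproduces to rounding. The 40 cannot be reproduced, because no effect size or SD is given.

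**Number of MCI cases (assumption).** The Background gives 17.2% MCI in T2DM. The article does not say who enters the ROC analysis, so I took two ends:

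- both case groups, evaluable: 2 × 40 = 80; 0.172 × 80 = 13.8, about 14 with MCI and 66 without;
- everyone enrolled: 3 × 53 = 159; 0.172 × 159 = 27.3, about 27 with MCI and 132 without.

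A lower rate outside T2DM would give fewer cases in each.

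**Precision of one AUC (Hanley-McNeil).** With A the AUC, m cases, n non-cases, Q1 = A/(2 − A) and Q2 = 2A²/(1 + A):

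SE² = [A(1 − A) + (m − 1)(Q1 − A²) + (n − 1)(Q2 − A²)] / (mn).

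For A = 0.75 the SE is 0.080 with 14/66 and 0.057 with 27/132. The 95% half-widths are 1.96 × 0.080 = 0.16 and 1.96 × 0.057 = 0.11.

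**Picking the best of four sequences.** I simulated binormal markers in the same subjects, 20,000 runs per setting. The mean shift for a marker with AUC A is √2·Φ⁻¹(A). One sequence is truly best and the other three have AUC 0.70. The AUCs and correlations are assumptions. A blind pick would be right 25% of the time.

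| MCI / not | Correlation | Best is 0.75: correct pick | Best is 0.80: correct pick | SD of paired difference (0.75 v 0.70) |
|---|---|---|---|---|
| 14 / 66 | 0.3 | 49% | 74% | 0.089 |
| 14 / 66 | 0.6 | 56% | 85% | 0.070 |
| 27 / 132 | 0.3 | 58% | 88% | 0.064 |
| 27 / 132 | 0.6 | 68% | 96% | 0.049 |

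Repeat simulations differ by about one percentage point, so the ranges are about 48 to 68% for a gap of 0.05 and 73 to 96% for a gap of 0.10. With 14 cases a 95% interval for the difference is about ±1.96 × 0.070 = ±0.14 to ±1.96 × 0.089 = ±0.17.

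**Combinations.** I took one informative sequence (AUC 0.70) and three that are pure noise, combined by logistic regression and scored on the data used for fitting (3,000 runs). The four-sequence combination had a higher AUC than every single sequence in about 92 to 93% of runs, with 14 cases and with 27.

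**Power of a paired comparison.** Approximate power is Φ(gap/SD − 1.96). With 14 cases and a gap of 0.05: Φ(0.05/0.089 − 1.96) = 8% and Φ(0.05/0.070 − 1.96) = 11%. At a gap of 0.10, where the SD is slightly smaller, it is 21 to 31%. With 27 cases it is 12 to 17% and 36 to 55%.

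**The case against.** The strongest reply is that this is a condensed article. A method for comparing AUCs is commonly left to an analysis plan, which is not shown, and the Discussion sentence is tentative. ROC performance is not a listed outcome, and nothing says that a sequence with a lower AUC is dropped. These points limit what can be claimed: the article does not show that no interval or test will be produced. They do not remove the concern. The article names a criterion, the highest AUC, and a consequence, the cut-offs, and its statistics section likewise picks the most sensitive parameters before drawing the curve. That criterion is poor as it stands.

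Three stronger readings are tempting, and the article does not support them.

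- A reader might infer that the chosen protocol is close to a coin toss. That fits only a true gap near 0.05 among four sequences. Even there the rule does about twice as well as a blind pick or better, and at a gap of 0.10 it is usually right.
- A reader might infer that the trial fails to test whether MRI adds to clinical data. The article makes no such claim. Its motive is an objective alternative to subjective cognitive tools, so a clinical reference model would be a new objective.
- A reader might infer that the article asserts multimodal imaging to be superior. Its wording leaves open that a single sequence comes first.

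It is also fair to say that a paired test would have little power here. That argues for showing the interval and for not naming a winner on a point estimate.

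**Conclusion.** The concern holds in limited form. As stated, the highest-AUC criterion cannot separate a better protocol from a lucky one. If combinations are scored on the data used to fit them, it will nearly always favour the combination.

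The size depends on assumptions that the article does not fix: the 17.2% rate applied beyond T2DM, the ROC population, the true AUCs, the marker correlation and same-data scoring of combinations. Under those used here, the criterion misses the best of four sequences in about 32 to 52% of trials at a gap of 0.05, and in about 4 to 27% at a gap of 0.10. The absence of a clinical reference model is not an error in the plan.

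**What to change.** Replace the highest-AUC criterion with the following:

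1. Report paired AUC differences with 95% confidence intervals (bootstrap or DeLong) between the sequences, and between the combined protocol and the single sequences.
2. Correct for optimism by cross-validation or bootstrap, repeating parameter selection and model fitting within each resample. Plain DeLong on combinations fitted to the same data is not enough, and neither is a comparison with a best single sequence chosen on those data without repeating that choice.
3. Describe a protocol as better only if the interval excludes zero. Otherwise report the protocols as not distinguished.
4. State who enters the ROC analysis and the expected number of MCI cases.

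A reference model from age, sex, education and HbA1c, all already collected, is an optional addition. With about 14 cases, its four terms leave 14 / 4 = 3.5 cases per term before any imaging marker is added.

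The cost is a few lines of analysis text and standard software, with no new data. The downside is that, with so few MCI cases, the trial will often be unable to name a best protocol.

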## Abbreviations

ALFF: Amplitude of low frequency fluctuation
CBF: Cerebral blood flow
3D-BRAVO: Three dimensional brain volume imaging
DKI: Diffusional kurtosis imaging
3D-pCASL: Three-dimensional pseudo-continuous arterial spin labeling
DTI: Diffusion tensor imaging
FAB: Frontal assessment battery
FLAIR: Fluid-attenuated inversion recovery
FPG: Fasting plasma glucose
HAS: Hamilton anxiety scale
HC: Healthy control
IFG: Impaired fasting glucose
IGT: Impaired glucose tolerance
MCI: Mild cognitive impairment
MMSE: Mini-mental state examination score
MNI: Montreal Neurological Institute
MoCA: Montreal cognitive assessment
OGTT: Oral glucose tolerance test
ReHo: Regional homogeneity
ROC: Receiver operating characteristic
rs-fMRI: resting-state functional magnetic resonance imaging
SDS: Self-rating depression scale
sMRI: structure magnetic resonance imaging
SPECT: Single-photon emission computed tomography
SPM12: Statistical parametric mapping 12
T2DM: Type 2 diabetes mellitus
T1WI: T1-weighted imaging
T2WI: T2-weighted imaging
WHOQOL: The World Health Organization quality of life assessment
